Eligible participants enrolled in this clinical trial will have a total of 28 visits. There will be 1 screening visits which will take place over the phone, 3 on-site visits (including 1 mask development visit, 1 mask delivery visit, and 1 very last follow-up visit) and 24 On-line visits (to take place over videoconference on Zoom platform); Baseline Visit (Visit 0), 20 days of the FES treatment sessions (Visits 1-20), and three post-stimulation visits (Visits 21-23). The screening Visit will take about 90- minutes, the on-site mask development visit will take 40 minutes and the mask delivery Visit will take 60-90 minutes. The baseline Visit (Visit 0) will take approximately 45 minutes, and treatment days (Visits 1-20) will take 60 min each (45 min for stimulation and 15 min for preparations). Sessions 5, 10, 15, and 20 will last about 105 minutes and will include similar clinical assessments/questionnaires to the baseline visit. The post-stimulation visits will take approximately 45 min. We estimate that the total participation duration will be approximately 33 to 35 hours.

Prior to the baseline visit, participants will undergo a screening evaluation that includes a medical/treatment history assessment and a confirmation of the MDD diagnosis. If all inclusion criteria are met, the mask development visit, the mask delivery visit, and the baseline visit will be scheduled. During Visit 0, medical assessments will be performed, and baseline assessments consisting of a semi-structured interview and self-report scales will be conducted. Once all baseline measures are collected, participants will be randomly assigned to one of two treatment arms:

- **ARM 1. 40 Hz FES:** 40 Hz Functional Electrical Stimulation (FES) stimulation, 45 mins per day for the duration of 4 weeks (20 sessions).
- **ARM 2. Sham FES:** 45 mins per day for the duration of 4 weeks (20 sessions).

Patients who miss a treatment visit, including due to statutory holidays, will be flagged in the database as non-adherent but will not be withdrawn from the study. They will still receive the entire treatment schedule but over a longer time period. However, if subjects miss more than two treatment days during treatment Days 1-20, they will be withdrawn.

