|------------------|-------------------------------------------------------------------------------------------------------------------------------------------------------------------------------------------------------------------------------------------------------------------------------------|------------------|------------|----------|---------------------------------------------|---|---|---|---|---|---|---|---|----|----|----|----|-------------------------------------------------------------------------------------------------------------------------------------------------------------------------------------------------------------------------------------------------------------------------------------------------------------------------------|----|----|----|----|----|----|-----------------------------------------|----|----|----|
|                  | Enrollment                                                                                                                                                                                                                                                                          | Mask development | Allocation | Baseline | Post Allocation: Randomized Treatment Phase |   |   |   |   |   |   |   |   |    |    |    |    |                                                                                                                                                                                                                                                                                                                               |    |    |    |    |    |    | Follow up Period (With no intervention) |    |    |    |

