| Mask design      |                                                                                                                                                                                                                                                                                     | X                |            |          |                                             |   |   |   |   |   |   |   |   |    |    |    |    |                                                                                                                                                                                                                                                                                                                               |    |    |    |    |    |    |                                         |    |    |    |
| Mask delivery    |                                                                                                                                                                                                                                                                                     |                  | X          |          |                                             |   |   |   |   |   |   |   |   |    |    |    |    |                                                                                                                                                                                                                                                                                                                               |    |    |    |    |    |    |                                         |    |    |    |

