**Table 1: Study Schedule**

## 6.2. Randomization and Blinding

Participants will be randomized in a 1:1 allocation to receive FES (active pattern) or FES (sham pattern). Block randomization will be computer-generated, and the samples will be stratified for sex, given the potential differences in response and tolerability in these groups. A biostatistician will generate the randomization schedule, to be administered by a research assistant who is not associated with the study and instructed not to divulge group assignments to the participants to allow for concealment.

Participants and most study staff will be blinded. Only the physical therapist will need to monitor the participant. Measures taken to prevent functional unblinding include sensory and non-patterned sham and delivering automated messages to both active and sham groups. We will also evaluate each participant's ability to discriminate what treatment they received after each session to assess blinding effectiveness.

We will randomize subjects to study arms (20 days active or 20 days sham) using a secure online randomization module on REDCap. The block size will be fixed, and study personnel will be blinded to the randomization block size. An independent assistant, external to the study, will manage the randomization of subjects. The subject number and treatment code will be assigned

after the subject details have been obtained. Based on this information, the independent assistant will assign a unique subject number and treatment code, which will dictate the treatment assignment for the subject. The patterns will be pre-programmed into the take-home device by the biomedical team.

An unblinded code sheet that matches these stimulation codes to the treatment arm will be kept by an external coordinator and will not be available to the study coordinator or research assistants. The unblinded code sheet will have the following information:

1. The initial identifier codes for all potential participants
2. Stimulation code: 6-digit numerical code for the stimulation session
3. Condition number: Numerical code for the condition
4. Condition name: Name of the condition

A copy of this code sheet with the condition name removed will be provided to the study coordinator and research assistants. These linked codes ensure that the study coordinator and research assistants are kept blinded to the type of treatment each participant will receive.

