#### Mask Delivery Visit:

The mold-printing and mask-making procedure will take 10-15 hours. We will use standard 3D printing technologies to print the designed mold geometry. After 3D printing the rigid plastic mold, we will cast the flexible mask with slots for affixing the electrodes to the desired locations of the mask surface facing the skin, and then run the cables for connection to the stimulation system through slits on the flexible mask. The mask will also be equipped with at least two hook-and-loop elastic band and Velcro fasteners passing around the back of the head to hold the mask on the face during the stimulation period. The mask will have a flexible nose wire extracted from commercially available surgical masks to better fit the mask around the subject's nose. The mask customized for the subject will then be ready for mounting on the subject's face to perform the targeted stimulation. We will deliver the customized mask during an on-site visit to the user with instructions about how to put the mask on and apply the stimulation.

Due to the customized design for each person with all components integrated into it, we expect that the process of wearing the mask and using it would be very straightforward. The instructions of use will be provided to the participants in both written and verbal formats. The participant will turn on the unit. There will be an external box with four switches for the four channels. The switches control the stimulation in the set-up phase. They will be in the set-up position at the start. Once all 4 channels are adjusted, the participant can switch all of the channels to the ready position to start the stimulation for the session. They should note down their suggested stimulation intensities for the 4 channels. A test of FES with mask will be done in this visit to walk the participant through the procedure and answer all the questions. Participants will receive the mask preprogrammed stimulator, and webcam at the end of this Visit.

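### Section 6.1 randomises after the Visit 0 baseline, but Table 1 puts allocation and handover of the programmed device before it, so baseline may follow allocation and a test stimulation

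*Protocol*

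**What the plan says.** The protocol gives the timing of allocation in several places.

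- **Section 6.1, text.** Randomisation follows Visit 0: "Once all baseline measures are collected, participants will be randomly assigned to one of two treatment arms". The same section lists the preceding visits in this order: "the mask development visit, the mask delivery visit, and the baseline visit will be scheduled".
- **Table 1 (Study Schedule).** The period headings read "Mask development | Allocation | Baseline | Post Allocation: Randomized Treatment Phase". The Allocation row and the "Mask delivery" row are both marked at timepoint -1. QIDS-SR-16, GAD-7, WHO-5, PSQI and FES Expectancy are first marked at timepoint 0. HAM-D-17 is marked at 0 and also at screening (-3).
- **Section 6.2.** The arm is carried by the device: "The patterns will be pre-programmed into the take-home device by the biomedical team". Section 7 says the same and places delivery of the stimulation system at the second on-site visit, which is mask delivery.
- **Section 6.3, Mask Delivery Visit.** "A test of FES with mask will be done in this visit", channel intensities are noted, and then "Participants will receive the mask preprogrammed stimulator, and webcam at the end of this Visit".
- **Section 6.3, Baseline Visit.** Baseline comes before the first FES visit and may be as late as the first stimulation day, provided it precedes that day's stimulation.
- **Section 14.2.** Baseline HAM-D-17 is the ANCOVA covariate and the start of the change score. Other continuous outcomes are handled in a similar way.

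**The concern.** Sections 6.1 and Table 1 cannot both be followed. The timing of randomisation relative to baseline is a basic design fact, and it decides whether the baseline values can have been influenced by arm.

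Under the Table 1 order, three things are at stake.

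- **The covariate and the change score.** A baseline taken after allocation, and after the participant has felt the device, can differ between arms because of allocation rather than chance. The arms are meant to feel different: section 7.1 gives 1-25 mA to activate muscles, and section 7.2 gives 1-8 mA at sensory level only.
- **Expectancy and blinding.** The first FES Expectancy rating would follow the test stimulation, so it would no longer be a clean pre-allocation measure.
- **Losses.** Anyone leaving between allocation and Visit 0 is lost after randomisation and has no Visit 0 scores. It is also unclear whether the test counts as the one FES treatment that section 14.2 requires for the modified intention-to-treat set.

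Baseline QIDS-SR-16 is also the reference for the worsening criterion in sections 6.1 and 10.3. A shifted baseline could therefore reach dropout, which is a primary outcome.

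**Working it through.** The plan gives no figure to reproduce here, so the main check compares the order of events. The arithmetic at the end only gives a sense of scale.

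**1. The two orders side by side**

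- *Section 6.1:* mask development, mask delivery, baseline (Visit 0), randomisation, sessions 1-20.
- *Table 1 with section 6.3:* screening (-3), mask development (-2), allocation with mask delivery and test stimulation (-1), baseline (0), sessions 1-20.

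The position of randomisation differs, and the two orders are incompatible.

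**2. Can the section 6.1 order be carried out as described?**

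Mask delivery precedes baseline even in section 6.1. The stimulator leaves mask delivery already programmed. Visit 0 and sessions 1-20 are by videoconference, and the only later on-site visit is the last follow-up (Visit 24). No step is described for programming or exchanging the device after a post-baseline randomisation. As written, the procedures support the Table 1 order.

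**3. Which stimulation before baseline could separate the arms?**

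- The pilot stimulation at mask development (-2) comes before allocation under either order and is the same for everyone, so it creates no between-arm difference.
- The test at mask delivery (-1) uses the mask, and the preprogrammed stimulator goes home from the same visit. It is probably arm-specific, but this is not stated. Section 7.3.2 has the user select mode and settings as instructed, and section 6.2 describes session stimulation codes. Both leave open that the arm is set later.

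**4. Scale, on stated assumptions**

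- Planned stimulation: 20 x 45 = 900 minutes.
- The length of the test is not given. If it were as long as a full session, it would be 45/900 = 5% of planned stimulation; a test of a few minutes would be under 1%.
- Suppose the test lowers the active arm's baseline by d points and leaves the final score unchanged. The change-score difference then moves by d toward the null, and the ANCOVA difference by slope x d.
- Upper value for d: section 3 reports an uncontrolled mean HAM-D improvement of 8.1 points after 10 sessions. If that were linear and wholly due to treatment, one session gives 8.1/10 = 0.81. So d ranges from 0 to 0.81.
- Assumed ANCOVA slope 0.3 to 0.8: 0.3 x 0.81 = 0.24 and 0.8 x 0.81 = 0.65. The adjusted difference moves by 0 to about 0.65 points; the change-score difference moves by 0 to 0.81.
- For comparison, take the pilot change SD of 5.26 in both arms with 10 per arm (t = 2.10 on 18 df). The 95% half-width of the difference in change is 2.10 x 5.26 x sqrt(2/10) = 4.9 points.

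These figures cover a direct effect of stimulation. The protocol gives nothing from which to size a shift caused by guessing the arm.

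**The case against.** The strongest case on the other side accepts the contradiction and disputes its weight.

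- **A reader might infer that baseline is post-treatment.** The protocol does not support that. Section 6.3 puts baseline before the first FES visit, so it precedes all 20 sessions. At most it follows allocation and a test of unstated length. This objection stands.
- **A reader might infer that people leaving before Visit 0 have no baseline at all.** Table 1 marks a HAM-D-17 at screening, and MADRS is scored there too. Section 6.4 does not list a screening HAM-D-17, so this needs confirming, but the absolute statement fails. Such leavers would also normally fall outside the modified intention-to-treat set, unless the test counts as a treatment. What remains is that they have no Visit 0 scores, and no earlier QIDS-SR-16, GAD-7, WHO-5, PSQI or expectancy rating is marked.
- **A reader might take the test stimulation to be arm-specific.** That is a strong inference, not a statement in the protocol.
- **A reader might expect a bias of a point or more on the HAM-D-17.** The protocol offers no basis for that. The illustrative range is under one point, against a half-width of about 4.9. WHO-5 refers to the past two weeks, so a short test is unlikely to move it much.
- **The primary outcomes are feasibility, tolerability and safety.** HAM-D-17 change is secondary and described as preliminary, and no efficacy decision rule rests on it. This is fair and limits the consequences.

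None of this settles which order applies, and no analysis can restore a pre-allocation baseline once visits have run in the other order.

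**Conclusion.** The protocol states the time of randomisation in two incompatible ways, and its device procedures follow the version that allocates before baseline. That conclusion rests on the text alone and is firm.

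Under the Table 1 order, the baseline HAM-D-17, the self-report scales and FES Expectancy are measured after allocation and after a test stimulation, though before session 1. They could therefore be affected by arm or by partial unblinding. This depends on the test using the assigned pattern, or on the participant otherwise sensing the arm; the first is probable but not explicit.

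The size is unknown and probably small. On the assumptions shown (a full-session test, a linear and wholly causal pilot effect, slope 0.3 to 0.8) the upper end is 0.24 to 0.65 HAM-D-17 points in the ANCOVA and 0.81 in the change score, toward the null. The case for acting is that the contradiction is plain and cheap to remove, not that a large bias has been shown.

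**What to change.** Set one order and use it throughout:

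1. mask development;
2. Visit 0 baseline assessments by videoconference;
3. randomisation in REDCap;
4. device programming;
5. mask delivery with test stimulation and handover;
6. session 1.

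Text to amend:

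- **Table 1:** move Baseline ahead of Allocation and mask delivery.
- **Section 6.1:** keep randomisation after baseline, but change the listed visit order, which now has mask delivery before baseline.
- **Section 6.3:** move the Baseline Visit ahead of mask delivery, and remove or reword the allowance for baseline on the first stimulation day. State whether the test uses the assigned pattern and whether it counts as an FES treatment for the modified intention-to-treat set.

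Cost: two existing visits change places. Device programming must wait for Visit 0, which may add a few days per participant. Section 6.3 gives 10-15 hours for making the mold and mask, so the videoconference can fall in that gap. One consequence to accept is that a participant who drops out at mask delivery, for example over fit, is lost after randomisation. That is already so under Table 1.

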**Table 1: Study Schedule**

## 6.2. Randomization and Blinding

Participants will be randomized in a 1:1 allocation to receive FES (active pattern) or FES (sham pattern). Block randomization will be computer-generated, and the samples will be stratified for sex, given the potential differences in response and tolerability in these groups. A biostatistician will generate the randomization schedule, to be administered by a research assistant who is not associated with the study and instructed not to divulge group assignments to the participants to allow for concealment.

Participants and most study staff will be blinded. Only the physical therapist will need to monitor the participant. Measures taken to prevent functional unblinding include sensory and non-patterned sham and delivering automated messages to both active and sham groups. We will also evaluate each participant's ability to discriminate what treatment they received after each session to assess blinding effectiveness.

We will randomize subjects to study arms (20 days active or 20 days sham) using a secure online randomization module on REDCap. The block size will be fixed, and study personnel will be blinded to the randomization block size. An independent assistant, external to the study, will manage the randomization of subjects. The subject number and treatment code will be assigned

after the subject details have been obtained. Based on this information, the independent assistant will assign a unique subject number and treatment code, which will dictate the treatment assignment for the subject. The patterns will be pre-programmed into the take-home device by the biomedical team.

An unblinded code sheet that matches these stimulation codes to the treatment arm will be kept by an external coordinator and will not be available to the study coordinator or research assistants. The unblinded code sheet will have the following information:

1. The initial identifier codes for all potential participants
2. Stimulation code: 6-digit numerical code for the stimulation session
3. Condition number: Numerical code for the condition
4. Condition name: Name of the condition

A copy of this code sheet with the condition name removed will be provided to the study coordinator and research assistants. These linked codes ensure that the study coordinator and research assistants are kept blinded to the type of treatment each participant will receive.

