### **5.3. Method of Recruitment**

The single study center will be the Interventional Psychiatry Program at St. Michael's Hospital, Unity Health Toronto (SMH, UHT). The subjects will be recruited from the Interventional Psychiatry Program at St. Michael's Hospital, Unity Health Toronto. The target recruitment rate is a total of 20 subjects recruited over 6 months. Considering our prior experience with this type of study, we do not anticipate any significant compliance issues. We note that the 5 sessions per week proposed here exceeds the schedule in the preliminary study by 2 sessions per week with the presence of a sham arm; we have included a conservative 15% dropout rate in our sample size calculations. However, a 5 session per week schedule is well tolerated in rTMS for MDD and in FES for stroke rehabilitation. Notably, since the intervention includes monitored home-based visits, treatment adherence will be known with 100% accuracy.

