### **12.4. Data Management Responsibilities**

The responsibilities designated to each member of the research team will be documented on the Delegation of Authority Form. The study coordinator and research assistants will be responsible for the informed consent process, review for eligibility, questionnaire administration, data entry, device administration, and e-CRF entries. The study coordinator will be responsible for AE/SAE documentation and reporting, while the investigator will be responsible for the AE assessment, review of the AE documentation forms, and overview of the research staff.

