### **14. Data Analysis**

#### **14.1. Sample Size Considerations and Study Feasibility**

For this pilot feasibility trial, we aim to recruit 20 participants in total.

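### A single fixed block size within sex strata at one site of 20 (Protocol 6.2) leaves some assignments foreseeable if earlier arms are recognised; randomly varying blocks are a cheap improvement

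*Protocol*

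**What the plan says.** Section 14.1 sets the size: "For this pilot feasibility trial, we aim to recruit 20 participants in total". Section 5.3 names a single centre. Section 6.2 allocates 1:1 and adds: "Block randomization will be computer-generated, and the samples will be stratified for sex". On the blocks themselves it says: "The block size will be fixed, and study personnel will be blinded to the randomization block size". The size is not given.

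Section 6.2 also contains safeguards. "An independent assistant, external to the study, will manage the randomization of subjects". The key linking codes to arms stays with an external coordinator, and both arms hear the same automated messages. Staff blinding is not complete, however: "Participants and most study staff will be blinded. Only the physical therapist will need to monitor the participant".

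Section 12.4 divides the work as follows: "The study coordinator and research assistants will be responsible for the informed consent process, review for eligibility, questionnaire administration, data entry, device administration". The roles that recruit are therefore also the roles that handle the device.

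Sections 7.1 and 7.2 describe the arms. Active stimulation runs over 1-25 mA and is meant to contract the muscles. Sham runs over 1-8 mA, is sensory only and follows a different pattern. Under Section 6.3, sessions take place by videoconference and are recorded, with the eye and mouth areas left open in the mask.

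**The concern.** With one fixed block size, once an arm has used up its places in a block, every remaining assignment in that block is determined. Concealing the size protects the list only while staff cannot guess it and cannot tell which arm earlier participants received. With 20 participants in two strata few sizes are practical, and the arms differ in intensity and pattern, so neither protection is complete.

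A recruiter who foresees the next arm in a sex stratum can hasten or delay a borderline participant, or present the study differently. With about ten participants per arm, one steered enrolment is 10% of an arm. The results exposed are the between-arm comparisons: dropout, compliance and adverse events in Hypotheses 1a and 1b, and the HAM-D-17 comparison in Section 14.2. Dropout or compliance proportions pooled over both arms do not depend on which arm a participant was steered into.

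**Working it through.** **Inputs from the protocol:** 20 participants (14.1), 1:1 allocation, two sex strata and a fixed block size (6.2), one site (5.3). The protocol gives no predictability figure, so there is nothing of its own to reproduce.

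**Assumptions:** block size 2, 4 or 6 (8 and 10 as a wider range); sex split 10/10 (range to 15/5); earlier arms in the stratum recognised before the next enrolment, except in step 6.

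**Step 1, complete blocks, size known.** In a block of size b = 2m, an assignment is forced once one arm has filled its m places. The expected number forced per block is 2m/(m+1), a share of 1/(m+1): 1/2, 1/3 and 1/4 for b = 2, 4 and 6 (1/5 and 1/6 for 8 and 10).

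**Step 2, strata of 10/10 with an incomplete last block.**
- b = 2: five blocks with 1 forced each give 5 per stratum, so 10.0 of 20.
- b = 4: two complete blocks give 2 × 4/3 = 2.67. The two leftover positions cannot be forced. Total 2 × 2.67 = 5.3 of 20.
- b = 6: one complete block gives 6/4 = 1.5. Of the four leftover positions only the fourth can be forced, when the first three agree: 2 × (3/6 × 2/5 × 1/4) = 0.1. Total 2 × 1.6 = 3.2 of 20.

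These are 50%, 27% and 16%. Over splits from 10/10 to 15/5, simulation gives 45-50%, 27-33% and 16-23%, so 16-50% overall. Sizes 8 and 10 give 8-17%.

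**Step 3, fixed size not known.** Let the observer know only that the size is 2, 4 or 6, start with equal weights and update after each recognised arm. With 10/10 strata, and learning within each stratum separately, the certain assignments are 0, 1.4 and 2.0 of 20 for true sizes 2, 4 and 6. If the observer pools what the two strata reveal, they are 0%, 10% and 12%, that is 0, 2.0 and 2.4 of 20. About 4 of 20 are predictable with more than 90% probability when strata are learned separately. If any even size from 2 to 10 is possible, 0-2.5% are certain for true sizes 2 to 6.

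**Step 4, sizes drawn at random from 2, 4 and 6, the set known.** About 0.6 of 20 are certain and about 1.2 of 20 exceed 90%. The expected difference between arm sizes is about 1 participant, similar to fixed blocks of 4 or 6. Fixed blocks of 2 in even strata have none.

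**Step 5, best guesses.** Expected correct guesses, against 10 of 20 by chance, are in the last column.

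| Scheme (10/10 strata) | Certain, of 20 | Over 90%, of 20 | Correct guesses, of 20 |
|---|---|---|---|
| Fixed 2, size known | 10.0 | 10.0 | 15.0 |
| Fixed 4, size known | 5.3 | 5.3 | 13.7 |
| Fixed 6, size known | 3.2 | 3.2 | 13.0 |
| Fixed, known only to be 2, 4 or 6 | 0-2 | about 4 | about 14 |
| Random 2/4/6, set known | 0.6 | 1.2 | 13.8 |

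**Step 6, late recognition.** If the most recent participant in the stratum has not yet been recognised when the next enrols, then even with the size known (65/35 sex mix assumed) the certain share falls to 0%, 7% and 6.5% for sizes 2, 4 and 6.

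**The case against.** The strongest reply is that the protocol does conceal the block size. A reader might infer that a quarter to a half of assignments are predictable with certainty as soon as earlier arms are recognised. The documents do not support that: the same sentence that fixes the size hides it from study personnel, and without it certainty falls to about 0-2 of 20. Even with the size known, blocks of 6 in 10/10 strata give 16%. This part of the reply stands.

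It is also fair that the comparison must rest on equal knowledge. Setting a fixed size that is known against random sizes that are not exaggerates the gain. When the observer knows only the set 2, 4, 6 in both cases, true blocks of 2 yield no certain assignments at all, so fixed is no worse on that measure. What remains on the equal footing is the drop in near-certain predictions, from about 4 to about 1.2 of 20. The number of correct guesses hardly moves.

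Recognition is not assured either. Both arms hear the same messages, participants smile voluntarily during stimulation, and a mask covers much of the face. Eligibility review by telephone and written consent at the first on-site visit both come before allocation, which Section 6.1 places after baseline and Table 1 at mask delivery. Treatment lasts 4 weeks and 20 participants enrol over 6 months (5.3) or 12 months (6.1), so participants are likely to overlap. Step 6 shows how much a single unrecognised arm removes. These points make the risk conditional; they do not remove it.

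**Conclusion.** The point holds as a conditional weakness. About 16-50% of assignments are forced only if the block size is 2 to 6, is known or inferred, and earlier arms in the stratum are recognised in time. If staff know only that the size is one of 2, 4 or 6, about 0-2 of 20 are certain and about 4 of 20 are predictable above 90%. Block size, sex split and recognition are all assumptions, since the protocol gives none of them.

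A fixed, concealed block size with external allocation is a defensible choice. Varying the size is a low-cost improvement on it.

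Two stronger readings should be resisted. One is that allocation concealment has failed: nothing in the protocol shows that recruiting staff know the size or the arms. The other is that staff could read future assignments from their copy of the code sheet, which keeps a condition number. Section 6.2 does not say whether that copy is issued complete in advance or whether one number marks one arm. Varying the blocks would not bear on that question in any case.

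**What to change.** In Section 6.2, replace the statement that the block size is fixed with: *Block sizes will vary at random (for example 2, 4 and 6) within each sex stratum, known only to the biostatistician who generates the list.* The list can be loaded into the REDCap module already planned.

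The cost is one protocol sentence and one parameter in the program that generates the list. The statistical price is small: an arm imbalance like that of fixed blocks of 4 or 6.

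Optionally, where existing staffing allows, Section 12.4 could provide that staff who watch stimulation do not carry out consent and eligibility review for later participants. This acts on recognition itself, which varying blocks leave untouched, but in a small team it may not be free.
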